#### Minimum detectable effect size

The number of participants will be constrained by the number of compounds in the study neighbourhoods that have received the sanitation intervention or meet the eligibility requirements for MapSan control compounds, most of which were previously enrolled in the MapSan trial. At the 24-month follow-up, an average of 2.5 children per compound were enrolled from 408 compounds.^34^ Compound-level intraclass correlation coefficients were generally less than 0.1 for individual pathogens, corresponding to cluster variances of ~0.05. We calculate the minimum detectable effect size (MDES) on individual pathogen prevalence with 80% power, 5% significance level and 0.05 compound cluster variance for a conservative scenario with 200 compounds per treatment arm and 2 children enrolled per compound (for 800 children total, 400 per arm), a moderate scenario of 220 compounds per treatment arm and 2.5 children enrolled per compound (550 children per arm, 1100 total), and a maximal scenario of 300 compounds per arm, 2.5 children per compound (750 children per arm, 1500 total).^108^ Across all scenarios, a minimum baseline (untreated) prevalence of 6–8% is required to reach 80% power for even the largest theoretical effect (nearly 100% reduction). The minimum detectable relative reduction in prevalence decreases (ie, smaller effect sizes are more readily detected) as pathogen prevalence increases towards 100% (figure 1). The difference between the scenarios on the multiplicative scale is relatively minor, with the relative reduction MDES largely driven by pathogen baseline prevalence. A pathogen with baseline prevalence below 15% must have its prevalence halved (PR<0.5) in order to attain 80% power, while a 25% reduction is detectable with 80% power for baseline prevalence of 34%–46% under the maximal and conservative scenarios, respectively. We expect the simultaneous consideration of multiple pathogens to reduce the MDES for the primary outcome pooled intervention effect by effectively increasing the sample size. Because this pooled effect is dependent on the prevalence of each pathogen considered and the correlations between them, we will conduct simulation analyses to characterise plausible MDES ranges for the pooled primary outcome treatment effect.^68 108^

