**Figure 1 F1:**
[figure not shown]
Range of minimum detectable effect sizes (shaded region) for the per cent reduction in pathogen prevalence with 80% power, 5% significance level and 0.05 cluster variance across three sample size scenarios. The upper edge of the shaded area represents a conservative scenario with 800 total participants (2 per compound, 200 compounds per arm) while the lower edge corresponds to a maximal scenario with 1500 total participants (2.5 per compound, 300 compounds per arm). A moderate scenario with 1100 total participants (2.5 per compound, 220 compounds per arm) is represented by the black curve within the shaded area. The vertical lines show the prevalence of a subset of pathogens assessed in control compound children during the 24-month follow-up in the original MapSan trial. Line colour indicates the specific pathogen and line pattern reflects the pathogen class. MDES, minimum detectable effect size; STH, soil-transmitted helminth.

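### The individual-pathogen detectable effects use a compound variance of 0.05 that does not fit the plan's own ICC below 0.1; the error is conservative and largest at low prevalence

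*Protocol article*

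**What the plan says.** The section on minimum detectable effect size in the protocol article links the 24-month data to the calculation in one sentence: "Compound-level intraclass correlation coefficients were generally less than 0.1 for individual pathogens, corresponding to cluster variances of ~0.05". The MDES for individual pathogens is then computed with "80% power, 5% significance level and 0.05 compound cluster variance", and the Figure 1 legend repeats the same setting: "80% power, 5% significance level and 0.05 cluster variance across three sample size scenarios".

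There are three scenarios:
- conservative: "200 compounds per treatment arm and 2 children enrolled per compound (for 800 children total, 400 per arm")
- moderate: "220 compounds per treatment arm and 2.5 children enrolled per compound (550 children per arm, 1100 total")
- maximal: "300 compounds per arm, 2.5 children per compound (750 children per arm, 1500 total")

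Three numerical conclusions follow. The first is a floor: "a minimum baseline (untreated) prevalence of 6–8% is required to reach 80% power for even the largest theoretical effect (nearly 100% reduction"). The second is that below 15% baseline prevalence, a pathogen reaches 80% power only if its prevalence is at least halved. The third is that a 25% reduction reaches 80% power at a baseline of 34% (maximal) to 46% (conservative).

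The pooled primary effect has no stated MDES. The section leaves it to simulation.

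**The concern.** For a binary outcome with prevalence p, the between-compound variance on the probability scale is ICC × p(1−p). It shrinks as p moves away from 50%, and at ICC 0.1 it can never exceed 0.1 × 0.25 = 0.025. A single value of 0.05 for all prevalences is therefore at least twice what the quoted ICC allows, and many times too large for uncommon pathogens.

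The three conclusions above are the only detectable effects that the plan states, and Figure 1 sets individual pathogens against the same curve. If the variance is wrong in a way that depends on prevalence, the curve has the wrong shape as well as the wrong height, most of all at its low-prevalence end.

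**Working it through.** **Inputs.** All are from the section on minimum detectable effect size: k compounds per arm and m children per compound (200 and 2; 220 and 2.5; 300 and 2.5), 80% power, 5% significance, ICC 0.1 as upper value, cluster variance 0.05. Assumption: the test is two-sided, since sidedness is not stated. The multiplier is then 1.960 + 0.842 = 2.802.

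**Step 1: reproduce the plan's figures.** Take 0.05 as a constant on the probability scale:

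Var(arm) = [0.05 + p(1−p)/m] / k; solve p0 − p1 = 2.802 × √(Var0 + Var1).

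Example, conservative scenario, p0 = 0.46, p1 = 0.75 × 0.46 = 0.345:
- p(1−p) is 0.2484 and 0.2260.
- The variance of the difference is [0.10 + (0.2484 + 0.2260)/2]/200 = 0.001686, so the SE is 0.0411.
- 2.802 × 0.0411 = 0.115, which equals the difference of 0.115.

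| Baseline prevalence needed | Maximal | Moderate | Conservative | Printed |
|---|---|---|---|---|
| 25% reduction | 33.2% | 40.0% | 46.0% | 34–46% |
| Halving | 13.4% | 16.2% | 18.5% | about 15% |
| 99.9% reduction | 5.6% | 6.7% | 7.2% | 6–8% |
| 95% reduction | 6.0% | 7.1% | 7.7% | 6–8% |

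The match is close but not exact. Other readings miss the floor: 0.05 as a logit-scale variance, or as a squared coefficient of variation, gives 1.0–1.9%. A constant ICC near 0.4 gives about 33–46% for a 25% reduction, but a floor of only 1.7–2.7%.

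**Step 2: what ICC does 0.05 imply?** ICC = 0.05 / [p(1−p)].
- p = 0.50: 0.05/0.25 = 0.20
- p = 0.15: 0.05/0.1275 = 0.39
- p = 0.08: 0.05/0.0736 = 0.68
- p = 0.0528: 0.05/0.0500 = 1.00; below this, 0.05 exceeds the whole binomial variance

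If 0.05 is instead counted on top of p(1−p), the ratio 0.05/[0.05 + p(1−p)] is still 0.17, 0.28 and 0.40 at the first three prevalences. On the logit scale, ICC 0.1 is a variance of (0.1/0.9) × π²/3 = 0.37, and 0.05 is an ICC of 0.05/(0.05 + 3.29) = 0.015.

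**Step 3: recompute with the stated ICC.** Var(arm) = p(1−p) × [1 + (m−1) × 0.1] / (k × m).

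| Quantity at ICC 0.1 | Maximal | Moderate | Conservative |
|---|---|---|---|
| Floor, near-100% reduction | 1.2% | 1.6% | 2.1% |
| Floor by Fisher's exact test | 1.2% | 1.6% | 2.2% |
| Halving detectable from | 6.8% | 9.1% | 11.7% |
| 25% reduction detectable from | 26% | 33% | 39% |

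The Fisher check uses effective sizes of 652, 478 and 363 per arm, and 6 events against 0 for significance.

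| MDES at baseline prevalence | Fixed 0.05 (maximal–conservative) | ICC 0.1 (maximal–conservative) |
|---|---|---|
| 50% | 18–23% | 15–21% |
| 15% | 46–58% | 34–44% |
| 8% | 75–93% | 46–60% |
| 5% | not reached | 57–73% |
| 3% | not reached | 71–88% |

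Where the plan puts 80% power for a 25% reduction, ICC 0.1 gives about 89% (46% baseline, conservative) and 92% (34% baseline, maximal).

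**The case against.** The scale is never stated, the cited method is not at hand, and the reproduction is loose in places: 33.2% against 34%, and a range of 13.4–18.5% against a single 15%. The sentence linking ICC and variance can even be made coherent. If 0.05 is a squared coefficient of variation, the ICC is 0.05p/(1−p), which is 0.05 at 50% prevalence and stays below 0.1 up to about 67%. This stands as a caution. The fault may lie in how 0.05 was applied rather than in the sentence itself. It does not rescue the printed figures, because that reading gives a floor of 1.0–1.9%, not 6–8%.

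The consequences are also limited, and this part of the objection stands in full. The section says that participant numbers are constrained by the available compounds, and the eligibility section aims to enrol every eligible child, so no sample size rests on the calculation. Individual prevalences are secondary outcomes. They are analysed with adjusted, partially pooled Bayesian models, whose power a two-proportion formula only approximates.

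A reader might infer that pathogens at 2–8% prevalence are well powered after all, so that null results for them would be wrongly put down to lack of power. The documents do not support that. At ICC 0.1, power to detect a halving is 20–32% at 2% prevalence, 28–45% at 3%, 43–66% at 5% and 50–75% at 6% (conservative to maximal). The lower floor concerns near-elimination only. The broad message that uncommon pathogens need very large effects survives.

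**Conclusion.** The point holds as an internal inconsistency in a descriptive power statement. The printed detectable effects are not those that follow from an ICC below 0.1. All three statements move: the floor by a factor of roughly three to five, the halving threshold from about 15% to about 7–12%, and the baseline for a 25% reduction from 34–46% to about 26–39%. The error is conservative, modest near 50% prevalence and largest where pathogens are rare.

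It would be a mistake to infer that the study is too small or that its primary analysis is compromised. Power is understated, recruitment is unaffected, and the pooled effect is touched only if the simulations reuse 0.05.

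The conclusion rests on three assumptions: 0.05 was applied as a constant on the probability scale (inferred from the match, not stated), the test is two-sided, and 0.1 is the upper value of the ICC. A lower ICC of 0.05 changes little: a floor of 1.1–2.0%, halving from 6.4–11.3%, and a 25% reduction from 25–38%. The normal approximation is rough at the floor.

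**What to change.** 1. State the scale of the cluster variance.
2. Recompute the MDES with between-compound variance ICC × p(1−p) in each arm, taking 0.1 as the upper ICC, or with a logit-scale variance matched to the ICC.
3. Redraw Figure 1 and replace the three statements. At ICC 0.1 (maximal to conservative) they become: a floor of about 1.2–2.1%, labelled as near-elimination only and confirmed by an exact method; halving from about 7–12%; and a 25% reduction from about 26–39%.
4. Say plainly that pathogens below about 5% prevalence still need very large reductions (about 57–73% at 5%, 71–88% at 3%).
5. Check that the simulations for the pooled primary effect do not carry the fixed 0.05 forward.

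The cost is one recalculation, one redrawn figure, a few sentences and a check of the simulation inputs. Recruitment and the analysis models stay as they are.

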**Figure 1 F1:**
[figure not shown]
Range of minimum detectable effect sizes (shaded region) for the per cent reduction in pathogen prevalence with 80% power, 5% significance level and 0.05 cluster variance across three sample size scenarios. The upper edge of the shaded area represents a conservative scenario with 800 total participants (2 per compound, 200 compounds per arm) while the lower edge corresponds to a maximal scenario with 1500 total participants (2.5 per compound, 300 compounds per arm). A moderate scenario with 1100 total participants (2.5 per compound, 220 compounds per arm) is represented by the black curve within the shaded area. The vertical lines show the prevalence of a subset of pathogens assessed in control compound children during the 24-month follow-up in the original MapSan trial. Line colour indicates the specific pathogen and line pattern reflects the pathogen class. MDES, minimum detectable effect size; STH, soil-transmitted helminth.

### Limitations

As an observational, cross-sectional evaluation of an existing intervention, this study faces a number of limitations that may impact the generalisability of our findings. By design, all of the study participants will have been born after the intervention was implemented in order to evaluate intervention impacts among individuals across a range of ages who have been exposed to intervention for their entire lives. However, there is potential for confounding bias in our estimates of the intervention impacts on child health, particularly concerning socioeconomic factors that may be associated with increased pathogen exposures. While non-randomised, the criteria for intervention and control compounds differed only by engineering considerations that we believe to be independent of the outcome. However, in the years since the intervention was implemented, the presence of the intervention itself may have influenced the desirability of the intervention sites and thus the socioeconomic status (SES) of their residents, particularly in light of the high population turnover previously observed after only 1–2 years. All analyses will be adjusted for a location-specific wealth index to account for potential differential SES between treatment arms,^104^ in addition to other prespecified covariates associated with enteric pathogen exposure that may plausibly be related to treatment status, but the possibility of unmeasured and insufficiently controlled confounding remains.

Because childhood diarrhoea is a leading cause of child mortality, selection bias arising from survivor effects may be present in our sample, particularly among older age groups.^109^ However, loss to follow-up due to mortality was exceptionally rare in the previous assessment—far less common than emigration, which was not previously differential by treatment arm.^34^ Our use of stool-based enteric pathogen detection as an objective primary outcome mitigates the potential for measurement bias^36^ and we are assessing multiple negative control outcomes to account for potential response bias in our secondary caregiver-reported outcomes.^78^ As a long-term evaluation of an existing intervention, the potential for exposure measurement error is low—interventions that have degraded substantially may shift results towards the null, but in so doing would represent a valid assessment of intervention sustainability.^110^ The potential for exposure misclassification among controls is higher, in that they may have independently upgraded to sanitation infrastructure comparable to the intervention. We are actively monitoring this possibility at all study sites; have prespecified criteria for identifying sites achieving such conditions; and will conduct sensitivity analyses with these sites excluded, considered as controls, and considered as equivalent to the intervention to characterise the impact of any such potential exposure misclassification among controls.

A key challenge is identifying an appropriate set of outcomes against which to evaluate the intervention; in this regard, we preferred inclusivity given the pathogens likely to be observed in our study setting, at the risk of unduly shifting our eventual results towards the null. This challenge persists, regardless of study design, so long as the study aims include assessing the effect of some condition or intervention on exposure to, or infection by, multiple pathogens that share a common route of transmission.^111^

### Contribution

Although observational, this study is unique in evaluating sanitation intervention effects at least 5 years after the intervention was implemented and up to 5 years after participants were borne into the intervention conditions. Previous studies have focused on WASH intervention impacts up to 2–3 years after delivery,^13 31–34^ which may be insufficient time to realise impacts.^42^ Furthermore, most previous studies have been conducted in rural settings, while we are investigating the long-term effects of an urban sanitation intervention that is broadly representative of the types of infrastructure improvements likely to be available in rapidly growing urban informal settlements in coming years. Finally, we use stool-based detection of multiple enteric pathogens as an objective outcome and propose a novel pooled estimate of the treatment effect across a prespecified outcome set to summarise the overall impact of the intervention on enteric pathogen exposure as the primary trial outcome.

### Ethics and dissemination

This study was approved by Comité Nacional de Bioética para a Saúde, Ministério da Saúde de Moçambique (FWA#: 00003139, IRB00002657, 326/CNBS/21; approved: 15 June 2021) and University of North Carolina at Chapel Hill Ethics Committee (IRB#: 21-1119; approved 19 August 2021) and was prospectively registered with ISRCTN on 16 March 2022 (https://doi.org/10.1186/ISRCTN86084138). We prespecified a statistical analysis plan that was deposited in a permanent online repository (https://osf.io/e7pvk/) prior to commencing enrolment. All protocol modifications will be submitted to, and approved by, the respective ethics committees prior to implementation and promptly updated on the ISRCTN registry.

Written, informed consent is obtained from the parent(s)/guardian(s) of each participant. Identifiable information is maintained separately to protect confidentiality and linked to surveys, stool, and environmental sample data by unique codes; the linking file to identifiable information will be destroyed on completion of the study and the study data and remaining biospecimens retained for fully deidentified ancillary analyses. Results will be presented to key stakeholders in Mozambique, including local and national government officials, public utilities, and NGOs, and published in open access peer-reviewed journals. On publication of study results, the underlying individual participant data will be fully deidentified and made freely available in the permanent online repository (https://osf.io/e7pvk/).
